## Abstract

**Introduction:**

Treatment of the node negative contralateral neck in oropharyngeal cancer (OPC) remains debated, with no clear consensus. Prophylactic contralateral neck treatment (either surgically or via irradiation) is generally recommended when the estimated risk of occult nodal metastasis is >20%. Unfortunately, patients undergoing bilateral neck treatment often require long-term supportive care for swallowing dysfunction. Reducing the impact of treatment on long-term quality of life is key in patients with OPC who have a good prognosis and tend to be young and fit at presentation. Lymphatic mapping and the use of free-hand single photon emission CT (fhSPECT) combined with sentinel lymph node biopsy is a novel approach to address this clinical need. The Lymphatic mapping Of Oropharyngeal Cancer trial aims to (a) validate a lymphatic mapping protocol in OPC using new technology (fhSPECT) with radiotracers and (b) establish lymphatic drainage patterns and the occult metastatic rate in the contralateral neck in OPC.

**Methods and analysis:**

The design is a prospective multicentre cohort trial to understand the lymphatic drainage pattern in 150 patients with OPC and unilateral neck metastases. The trial has two phases: (1) *imaging phase (n=75)*—aim: develop an imaging protocol to establish the lymphatic drainage pattern in a population of patients with proven unilateral neck metastasis from OPC. The intervention will involve peritumoural injection of radiotracer followed by fhSPECT scan under general anaesthesia (GA) (at time of examination under anaesthetic). A SPECT/CT scan (gold standard for lymphatic mapping) will be carried out subsequently as a comparator. The primary outcome is the rate of contralateral drainage. Secondary outcome is the accuracy of fhSPECT versus SPECT/CT. The number of contralateral nodes on SPECT/CT will be used as the denominator in calculating the sensitivity of fhSPECT in independently verified images. fhSPECT should achieve sensitivity >94%. A minimum number of 20/75 patients will be required to demonstrate contralateral drainage to proceed to the surgical stage. An imaging substudy (n=20) aims to develop a secondary imaging protocol in the event of <94% sensitivity of intraoperative fhSPECT. To investigate the sensitivity of outpatient imaging (single injection of radiotracer and SPECT/CT) compared with gold standard (SPECT/CT from initial imaging phase) and the acceptability of outpatient injection compared with under GA. Twenty patients from the imaging phase with easily accessible tumours will be invited to undergo a second imaging; (2) *Surgical phase (n=75)*—aim: demonstrate the utility of surgically staging the contralateral neck using sentinel node biopsy (SNB). The primary outcome of this surgical phase is the occult metastatic rate of contralateral nodes (positive SNB). The contralateral drainage rate will be identified during the imaging phase, with an expected SNB positive rate of excised nodes ranging from 25% to 40%.

**Ethics and dissemination:**

The outcome of this trial will provide a validated protocol and evidence to inform the design of future research in which management of the contralateral neck is based on surgical staging. Ethical approval was granted by the Yorkshire & The Humber-South Yorkshire Research Ethics Committee (REC ref: 20/YH/0111). Results from the trial will be presented to the scientific community at appropriate meetings and international journals. Patients and the public will be informed via patient groups, cancer charities and social media/press releases.

**Trial registration number:**

NCT04498221.

STRENGTHS AND LIMITATIONS OF THIS STUDYTrial testing new technology to inform patient-specific treatment in a rapidly increasing tumour group (oropharyngeal cancer).Novel design incorporating in-built protocol development informs methodology of later stages of the trial.Interventions are specifically designed to fit into the current clinical pathway, paving the way for adoption in phase III trials.Reliance on technology may limit applicability in resource-poor settings.

## Introduction

### Background and rationale

#### Clinical need

 The Lymphatic mapping Of Oropharyngeal Cancer (LOOC) trial was developed to address patient concerns and published evidence showing an increasing unmet need in the treatment of patients with oropharyngeal cancer (OPC).^1^,^5^ Like other head and neck cancer subsites, OPC spreads to regional lymph nodes (LN) in the neck. Studies show that there is no consensus on the optimal treatment for the clinically node-negative contralateral neck in patients presenting with an OPC and unilateral neck metastasis. Most evidence is based on case series comparing the outcomes of unilateral versus bilateral treatment, with significant heterogeneity of the modality used (conventional/robotic surgery, conformal radiation or intensity-modulated radiation).^6^,^8^ However, all these studies show that morbidity (ie, dysphagia, feeding tube dependency, taste, xerostomia and neck lymphoedema) is significantly improved when only one side of the neck is treated.^9^,^12^ The reason for upfront treatment of the contralateral neck is to control occult metastases that are not detectable by routine staging imaging.

LOOC is an early phase oncology imaging trial, which will evaluate the utility of new technology to detect occult metastasis, thus accurately staging the contralateral neck. The results can then be rapidly translated to late phase prospective clinical trials in which treatment decisions can be based on the outcome of the validated protocol developed in LOOC.

#### Improving health outcomes in the National Health Service

Treatment of OPC is associated with significant morbidity. Traditionally, prophylactic treatment of the contralateral clinically node-negative neck is undertaken when the estimated risk of involvement is >20%.^13^ Patients undergoing bilateral neck treatment often require long-term supportive care for swallowing dysfunction because of changes to the swallowing-related organs (pharyngeal muscles, larynx, salivary glands and oesophagus).^11 12 14 15^ Dependence on feeding via gastrostomy or very limited oral diet is common. Reducing the impact of treatment on long-term function is key in patients with OPC who, in the case of human papillomavirus (HPV)-positive disease, have a good prognosis and tend to be younger and fit at presentation.^10 16^

Unilateral neck treatment has a clear benefit in protecting swallow function and thus improving quality of life. This trial is the first step in developing a technique to accurately stage the contralateral neck and thus spare the majority of patients from undergoing unnecessary treatment to the unaffected neck. If successful, this has major implications for improving survivorship for these patients, who are increasing in number with rising incidence of the disease. The impact for the National Health Service (NHS) will be immediate and long-lasting. Surgical time and inpatient stay will be reduced, as will acute admissions for dehydration during radiotherapy. Fewer patients will require percutaneous feeding, thus reducing complications. The impact on allied health professionals—speech and language therapists and dietitians including provision of dietary supplements will also be reduced. Furthermore, by developing a reliable imaging protocol for lymphatic mapping of deep tumours in LOOC, there will be easy translation to other head and neck cancers such as salivary gland, thyroid and larynx. There may also be translation to other deep body cavity tumours such as the lung and prostate gland, where there is controversy about the exact extent of nodal resection required, and nodal relapse is a major cause of treatment failure.

#### Justification for trial and comparators

The mechanism of reliability of lymphatic mapping to sentinel nodes was first described in 2007.^17^ Functional lymphatic imaging studies were undertaken in tumour and control footpads of mice. Tracer showed in the sentinel node within 2 min of injection compared with 30 min for the control. Histologically, sentinel nodes had c-Myc oncogene overexpression stimulating VEGF-C and VEGF-D to induce lymphangiogenesis in the node, causing a 23-fold increase in lymphatic tracer drainage. Lymphatic mapping reveals an active premetastatic process directing lymphatic flow to specific nodes. Human studies in oral cancer showed patients injected and imaged on two separate occasions a week apart had drainage to identical nodes.^18^

The LOOC trial will allow a choice of lymphatic mapping radiotracer, 99mTc-human albumin colloidal particles or 99mTc-Lymphoseek. 99mTc-human albumin colloidal particles are standard radiotracers, which accumulate within LN. These have a large body of evidence supporting efficacy in the mapping of sentinel nodes from oral cancer and more recently have been used to map lymphatic drainage in patients with cN0 OPC under general anaesthetic.^19^ In this study, patients were imaged by single photon emission CT (SPECT)/CT 3–6 hours postinjection with a contralateral drainage rate of 20%.

Lymphoseek has additional properties to aid retention in the sentinel node via binding to macrophage CD206 mannose receptor. The advantage of rapidly clearing the injection site while selectively retaining the substance in the sentinel node is crucial in LOOC, where the goal is to image the sentinel nodes in the operating theatre within minutes of injection. Scatter and ‘shine-through effect’ in traditional tracers can impair immediate imaging, but Lymphoseek has not been compared with traditional tracers within the intraoperative setting. Over a longer protocol, Lymphoseek has shown impressive results in reducing the false negative rate for sentinel node biopsy (SNB in oral tumours from 9% to 2.56%. Due to licensing arrangements, Lymphoseek is only intermittently available in Europe; therefore, the LOOC trial pragmatically allows investigators the choice of Lymphoseek or a standard colloid tracer. This protocol allows for ad hoc interim analysis to ensure there is no significant difference in the total number of nodes and contralateral nodes identified by each tracer.

Review of the literature reveals a small number of case reports using freehand SPECT (fhSPECT) for intraoperative SNB. In one series, 23 patients with oral cancer had a 98% sentinel node detection rate by fhSPECT. Another series of 66 patients with oral cancer identified 94% of the sentinel nodes by fhSPECT. Drug posology, specifically radiation dose, is considered similar with Lymphoseek and 99mTc-human albumin colloidal particles. The research team has performed a blinded study comparing intraoperative sentinel node imaging fhSPECT with pre-operative SPECT/CT in 50 patients with oral cancer. SNB using fhSPECT alone was superior to SPECT/CT (false negative rate 5.3% vs 15.8%, respectively).^20^ Currently, there are no reports using Lymphoseek or fhSPECT in OPC, but the outlined data above are used as proof of concept.

## Methods and analysis

### Objectives

LOOC is a phase II surgical imaging trial for OPC. The overarching aim and objective is to establish the lymphatic drainage pattern and occult metastatic rate in the contralateral neck of patients with OPC.

The trial is divided into two phases—imaging and surgery (figure 1).

**Figure 1 F1:**
[figure not shown]
Trial design and patient care pathway of imaging phase (above) and surgical phase (below) with STOP GO:NO GO decision at trial mid-point. fhSPECT, freehand single photon emission CT; GA, general anaesthesia; OPC, oropharyngeal cancer; SNB, sentinel node biopsy.

#### Imaging phase (n=75)

Objective: imaging protocol validation and establishing drainage pattern for patients with OPC with unilateral neck metastases.

##### Imaging substudy

Objective: to develop an alternative imaging protocol in case of failure of fhSPECT.

### Surgical phase (n=75)

Objective: feasibility of surgical staging of the contralateral neck in OPC with unilateral neck metastases.

### Trial design

LOOC is a multicentre prospective non-randomised phase II surgical imaging trial. This trial comprises two stages. Patients with newly diagnosed OPC with cervical metastasis will be considered for recruitment. The patient care pathway is shown in figure 1. The trial duration per participant is 4 weeks, with an estimated total trial duration of 54 months.

### Trial setting

The trial is being conducted in the secondary care hospital setting, within five high-volume UK head and neck (H&N) cancer sites—defined as a centre which sees over 100 new OPC diagnoses per year. Additional sites will act as participant identification centres in a ‘hub and spoke’ model, that is, smaller hospitals that refer into a tertiary cancer centre.

### Eligibility criteria

#### Inclusion criteria

Adults aged 18 or over.New diagnosis of OPC—all anatomical subsites and HPV status accepted.Unilateral metastatic nodes equating to American Joint Committee on Cancer tumour, node, metastasis (TNM) 8th edition clinical staging N1-N2b for p16-negative patients, and N1 for p16-positive patients.

#### Exclusion criteria

Suspicious bilateral nodes on imaging.Previous radiotherapy or surgery to the neck.Second primary oropharyngeal tumours.Distant metastasis (eg, lung, bone).Pregnancy and lactation.Inability to give informed consent.Allergy to lymphatic tracers.

### Planned interventions

The planned interventions in both the imaging and surgical phase of the LOOC trial are intended to occur opportunistically during the standard patient care pathway. When patients undergo an examination under anaesthesia (EUA) as part of surgical planning, or dental extractions under general anaesthesia (GA) prior to planned radiotherapy, the LOOC trial interventions will be conducted under the same GA procedure.

### Imaging phase

Four submucosal peritumoural injections of radiotracer are administered under direct/endoscopic vision during EUA.After 15 min drainage, fhSPECT scan is undertaken (declispeSPECT, Surgiceye). Separate scans of both the contralateral and ipsilateral neck are taken.Following recovery (and up to 24 hours later), conventional SPECT/CT is undertaken (gold standard imaging).

#### Imaging substudy

A subgroup of patients from the imaging phase (n=20) whose tumour is easily accessible without a GA (ie, clearly visible intra-orally) will be recruited to the imaging substudy. It is mandatory that patients recruited to the imaging substudy demonstrated nodal drainage on SPECT/CT (desirable if this was contralateral but not essential).

In the outpatient setting, 4–10 days after the initial imaging phase, a topical anaesthetic spray will be applied to the tumour, followed by a single injection of radiotracer placed directly into the tumour.This will be followed by a SPECT/CT and a questionnaire assessing the acceptability of this outpatient-based procedure.

Due to interruptions in Lymphoseek tracer supply in the UK during the trial period, coupled with widespread staffing pressures on radio-pharmacy and nuclear medicine departments, a pragmatic decision has been made to add the choice of 99mTc-human albumin colloidal particles as one of the radiotracers allowed for this trial. There have been no high-quality head-to-head comparisons of 99mTc-human albumin colloidal particles and Lymphoseek in any tumour group, although small studies have shown that Lymphoseek may identify more sentinel nodes but without impact on the number of positive nodes identified.^21 22^ No studies report the sentinel node identification rate in 99mTc-human albumin colloidal particles or Lymphoseek under 1 hour post-injection. Thus, we will seek to compare sentinel node identification rate on fhSPECT in two groups of patients to ensure there is no gross disparity at this early stage of lymphatic mapping. If 99mTc-human albumin colloidal particles do not match Lymphoseek performance (sentinel node identification rate at up to 30 min postinjection), we will revert to Lymphoseek as the sole tracer.

#### Surgical phase

The surgical phase is planned to follow immediately from the imaging phase if specified outcomes are met. The precise surgical protocol is to be informed by outcomes of the prior imaging phase. Either:

Intraoperative peritumoural tracer injection and fhSPECT imaging of contralateral sentinel node in theatre under a single GA.

or

Single intratumoural injection in the outpatient setting, followed by conventional SPECT/CT.

Either of the above is followed by an SNB (as per standard protocol)^23^ of contralateral nodes during EUA. As per accepted evidence, the presence of viable individual tumour cells or greater is considered metastatic nodes.^24^ The result of the SNB will be discussed with the patient and the oncology team prior to further treatment, but the recommendation will be based on the decision of the multidisciplinary team (MDT). This trial is not powered to recommend changes in treatment based on the SNB result.

#### Subsequent assessments and procedures

The trial procedures are very safe, but all patients will be screened for adverse reactions following the final scan or the day following SNB and all complications will be reported according to the following protocol.

#### Definition of end of trial

The expected duration of the trial is 4 years from recruitment of the first participant. The end of the trial is the date of the last follow-up of the last participant.

The trial will be stopped prematurely if:

This is mandated by the ethics committee.Following recommendations from the sponsor.Funding for the trial ceases.The Chief Investigator (CI), in consultation with the clinical and scientific lead, decides that sufficient biopsies and data have been obtained to fulfil the scientific objectives of the trial.

The Research Ethics Committee (REC) will be notified in writing within 15 days if the trial has been concluded or terminated early.

### Discontinuation/Withdrawal of participants

Participants will be free to withdraw from the trial at any time. No data or follow-up information will be collected in relation to participants from the date of withdrawal. The decision of a participant to withdraw from the trial will be recorded in the case report form (CRF). All recorded data and samples processed prior to the date of withdrawal of consent for trial participation will remain in the trial database and continue to be analysed as per trial protocol. In line with General Data Protection Regulations (GDPR), participants’ rights to access, change or move their information are limited, as these need to be managed in specific ways in order for the research to be reliable and accurate. On withdrawal from the trial, information already obtained will be kept, and no new data from the date of withdrawal will be held.

### Outcomes

#### Imaging phase

Primary outcome:

Rate of contralateral drainage. fhSPECT and SPECT/CT images reviewed by two independent assessors. Sum of non-duplicated contralateral hotspots taken as the true contralateral drainage rate. Minimum of 20/75 patients must demonstrate contralateral drainage to proceed to surgical stage.

Secondary outcome:

Accuracy of fhSPECT compared with SPECT/CT. Number of contralateral nodes on SPECT/CT used as denominator in calculating sensitivity of fhSPECT by independently verified images.

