#### Imaging phase outcome measure data collection

Each assessor fulfils a CRF per case with three questions:

Are there contralateral nodes on SPECT/CT? No/Yes (record neck level).Are there contralateral nodes on fhSPECT? No/Yes (record neck level).Do the contralateral nodes co-localise? Yes/No.

If contralateral nodes are shown in SPECT/CT but not on fhSPECT, this will be recorded as a false negative result (unless these can be attributed to second echelon nodes) for fhSPECT and vice versa. Contralateral drainage on either modality will be recorded as a true positive result. fhSPECT should achieve sensitivity >94% compared with SPECT/CT.

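### The second-echelon exemption covers only nodes that fhSPECT misses; the drainage rate, the 20/75 count, the true-positive rule and the stated sensitivity denominator carry no matching condition

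*Protocol article*

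**What the plan says.** Under Outcomes, Imaging phase, the primary outcome is the rate of contralateral drainage: "Sum of non-duplicated contralateral hotspots taken as the true contralateral drainage rate". The go rule follows directly: "Minimum of 20/75 patients must demonstrate contralateral drainage to proceed to surgical stage". The secondary outcome is the accuracy of fhSPECT: "Number of contralateral nodes on SPECT/CT used as denominator in calculating sensitivity of fhSPECT by independently verified images". None of these three sentences mentions echelon.

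Imaging phase outcome measure data collection brings echelon in once. For a contralateral node that only SPECT/CT shows, the rule reads: "this will be recorded as a false negative result (unless these can be attributed to second echelon nodes) for fhSPECT and vice versa". The next sentence has no such condition: "Contralateral drainage on either modality will be recorded as a true positive result". The three assessor questions listed there cover presence on each modality (with neck level) and co-localisation. The same section sets a sensitivity target above 94%. The Abstract ties a result below 94% to the fallback imaging protocol.

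For the surgical phase, one route is described as "fhSPECT imaging of contralateral sentinel node in theatre under a single GA"; the other is an outpatient injection with SPECT/CT. Sentinel node biopsy follows either route. Table 3 plans removal of the contralateral nodes seen on imaging and sets no echelon limit.

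**The concern.** The exemption shows that the protocol expects some contralateral SPECT/CT nodes to be second echelon and does not hold fhSPECT to finding them. The timing makes this plausible: fhSPECT is done 15 minutes after injection and SPECT/CT up to 24 hours later. The same node nevertheless stays in the hotspot sum, can qualify a patient for the 20/75 count, and is still part of the stated sensitivity denominator.

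Two decisions are exposed.

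- **Choice of imaging route.** The question of echelon arises only where fhSPECT has missed a node. A second-echelon node that fhSPECT does show is kept as a hit. The exemption can therefore raise sensitivity but never lower it.
- **Start of the surgical phase.** The 20/75 count is meant to show that enough patients have something to biopsy on the contralateral side. A patient whose only contralateral uptake is late and second echelon would count towards it, yet might show nothing in theatre under the fhSPECT route.

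**Working it through.** **1. The plan's own figures.** The Sample size section expects 96% agreement in 75 patients. That is 72/75, with an exact 95% CI of 88.8% to 99.2%, width 10.4 points (stated: about 10%). The exact one-sided 5% test against 88% rejects at 71 or more (size 4.5%), with power 81.9% at 96% (stated: 80%). These figures reproduce. They concern agreement and do not settle how echelon is treated. The go threshold is 20/75 = 26.7%, inside the 20%–30% of surgical-phase patients expected to have contralateral sentinel nodes.

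**2. The rules side by side.**

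| Rule | Section | Echelon condition |
|---|---|---|
| Hotspot sum (primary rate) | Outcomes | none |
| 20/75 patients | Outcomes | none |
| Sensitivity denominator | Outcomes | none (all contralateral SPECT/CT nodes) |
| True positive | Data collection | none |
| fhSPECT false negative | Data collection | second echelon excused |

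**3. Direction of the effect on sensitivity.** Of the contralateral SPECT/CT nodes, let F be first echelon, of which fhSPECT shows f, and let S be second echelon, of which it shows s.

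- All nodes, no exemption: (f + s)/(F + S)
- First echelon only: f/F
- As written, excused misses removed from the denominator: (f + s)/(F + s)
- As written, excused misses kept in the denominator but not counted as misses: (f + S)/(F + S)

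Since f ≤ F and s ≤ S, neither as-written figure is ever below either of the two consistent ones. With removal, the as-written figure equals the first-echelon figure if s = 0 or f = F.

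**4. Illustration (20 nodes is an assumption).**

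- Two misses, neither excused: 18/20 = 90%, below the criterion.
- One excused and removed: 18/19 = 94.7%, above it.
- One excused and kept: 19/20 = 95%, above it.

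With one genuine first-echelon miss, the first-echelon figure is (F − 1)/F. It exceeds 94% only if F is at least 17 (16/17 = 94.1%; 15/16 = 93.75%). The as-written figure passes whatever F is.

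**5. Effect on the go rule.** The count is of patients, so take X ~ Binomial(75, p), where p is the first-echelon rate plus the proportion whose only contralateral hotspot is second echelon. Both parts are assumed.

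| Assumed first-echelon rate | Assumed second-echelon-only | P(X ≥ 20) |
|---|---|---|
| 20% | 0 | 10.0% |
| 20% | 2 points | 19.9% |
| 20% | 4 points | 33.5% |
| 25% | 0 | 41.2% |
| 25% | 2 points | 57.0% |

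If every second-echelon node lies in a patient who also shows a contralateral first-echelon node, the probability does not change. The node-level hotspot sum is raised in either case.

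**The case against.** The two outcomes ask different questions. Contralateral second-echelon uptake is real contralateral drainage, and it is reasonable not to blame a 15-minute scan for a node that fills hours later. That second-echelon nodes count towards the rate is inferred from a missing exclusion, not from an express statement. Table 1 describes the SPECT/CT as imaging of sentinel nodes, so a sentinel-only reading is open. This is also a condensed article, and reading rules may sit in the full protocol or a reading manual.

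These points limit the size of the problem. They do not explain why the exemption reaches only the nodes fhSPECT misses. The article itself fixes the true-positive rule, the false-negative rule and the denominator, and applies echelon to one of the three. Statistical methods has the assessors consider each pair of scans, so as described the attribution can be made knowing that fhSPECT missed the node.

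Four stronger readings are tempting, and the document supports none of them.

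- **That one node always eases both criteria.** The go count moves only if the node is the patient's sole contralateral hotspot.
- **That the 94% criterion is a second condition for starting surgery.** The explicit numerical rule for proceeding is 20/75. The 94% figure mainly selects the imaging route, although the Surgical phase section refers generally to outcomes being met.
- **That the 20% in Justification for trial and comparators is a first-echelon rate.** It is given only as a contralateral drainage rate on SPECT/CT at 3–6 hours. If it covers all uptake, adding a second-echelon increment to it would double count.
- **That such patients add nothing to the biopsy yield.** Table 3 has no echelon limit, and under the SPECT/CT route the node could be seen and removed.

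**Conclusion.** The inconsistency stands as a matter of text: a SPECT/CT-only contralateral node can be true drainage and yet not a miss, and how an excused node enters the denominator is not fixed.

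For sensitivity the direction is certain: the rule as written can only match or exceed a consistent rule. The size depends on unknown node counts. With about 20 nodes, one excused node is worth 4.7 to 5 points against the stated all-node denominator, enough to cross 94%. Against a first-echelon target, the excess with removal is zero if fhSPECT shows no second-echelon nodes, and grows as it shows more.

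For the go rule the effect is conditional. It needs patients with a second-echelon node as their only contralateral hotspot, whose frequency the document does not give and which may be zero. The rise from 10% to 20% or 34% rests wholly on the assumed 20% base and the assumed 2 or 4 points. It shows only that a threshold inside the expected range can be decided by a few patients. The point merits a change because recruitment is under way and the change is small.

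**What to change.** - Class every contralateral SPECT/CT node once as first or second echelon, whether or not fhSPECT showed it, by a pre-set reading rule applied blind to the fhSPECT result.
- Use that class consistently in the drainage rate, the 20/75 count, the true-positive rule, and the numerator and denominator of sensitivity.
- Report the drainage rate and the go count with and without patients whose only contralateral hotspot is second echelon.
- Reconcile the Surgical phase section, which speaks of the sentinel node, with Table 3, which speaks of nodes seen on imaging, on whether second-echelon nodes fall within the surgical phase. Which it should be is for the investigators.

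The cost is one field on the assessor form, a written reading rule with a way to settle disagreements, and a sentence in the outcome definition. The reading rule is the real work, because the main imaging phase has a single SPECT/CT, up to 24 hours after injection, from which to judge echelon. The reported drainage rate and sensitivity may be slightly lower, and a go decision slightly less likely.
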